#### Statistical power

Power is simulated using a mixed effects linear model similar to model (4) for the KDIS scale with *β*_1_ = *β*_12_ = 0 and dropping *g*_1_(*t*;ψ) giving an assumption for simplicity of no secular trend:5$$ E\left({Y}_{\mathrm{i}\mathrm{t}}\Big|\ {b}_{\mathrm{i}0},\ {b}_{\mathrm{i}1}\right) = {\beta}_0 + {b}_{\mathrm{i}0} + {\beta}_2{X}_{\mathrm{i}2} + {b}_{\mathrm{i}1}t + {\beta}_3{X}_{\mathrm{i}\mathrm{t}3} $$with *X*_it3_ = (*t*-1)/3 for *t* = 1, 2, 3, and 4. Model (5) differs from model (4) in that we model 3-month averages of KDIS scales producing quarterly data, in accordance with preliminary data reported in Figure 2 of Halladay et al., which is as follows: electronic health record (mean 2.78, sd = 3.17); care protocols (mean 1.71, sd = 4.37); planned care (mean 2.16, sd = 3.84); and self-management support (mean = 1.38, 3.67). It follows their variances are 10, 19.1, 14.7, and 13.5, respectively [15]. Model (5) assumes that the intervention effect on KDIS is linear in time during the yearlong implementation period; under this model, the main hypothesis is an overall positive change in expected outcome between 12 months post-intervention and 3 months post-intervention (*β*_3_ > 0). For power calculations, we set *β*_0_ = 2, *β*_2_ = 0.5, *β*_3_ = 1.0, *σ*_0_^2^ = 5 (or 8), *σ*_1_^2^ = 4, *σ*_01_ = −2 and *σ*_e_^2^ = 5 (or 8). Then, under the random coefficients model, Var(*Y*_it_) = *σ*_0_^2^ + *σ*_1_^2^t^2^ + 2 t *σ*_01_ + *σ*_e_^2^. Additional file 3 shows that power to show an effect of intervention on KDIS scales exceeds 85 % under the assumptions.

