## Measures

*Implementation support*. We will measure primary care practice support intensity as the percentage of contacts with a practice that are in-person. We will also report the actual number of in-person contacts and number of total contacts to account for variability in contacts across practices. We will also track frequency, mode, and duration of contact with academic detailers, as well as number and type of staff per practice attending collaborative meetings.

*Practice capacity for QI* encompasses two constructs. The first construct, change process capability, refers to a “state of preparedness for change that is influenced by the organization’s previous history of change, its plans for continuous organizational refinement, and its ability through its social and technical systems to initiate and sustain that change” ([10], p. 193). We will measure this construct using the Change Process Capacity Questionnaire (CPCQ) [10]. The second construct, adaptive reserve, refers to “the practice relationship infrastructure; alignment of management functions in which clinical care, practice operations, and financial functions and reflect a consistent vision; facilitative leadership; teamwork; sense-making; a positive work environment; and a culture of learning”([11], p. S37). We will measure this construct using the Practice Adaptive Reserve scale [11, 12].

*Organizational readiness for change* refers to the extent to which organizational members are psychologically and behaviorally prepared to implement change [6, 7, 13]. We will measure readiness using the Organizational Readiness for Implementing Change scale [13].

*Implementation policies and practices* are the strategies that an organization puts into place to support innovation use [9, 14]. We will measure implementation policies and practices using the Key Drivers of Implementation Scales (KDIS) [15]. PFs will rate the extent of practice implementation of the four key drivers using a 5-point, behaviorally-anchored scale. Table 2 offers an example of the KDIS for planned care.

**Table 2 Tab2:** Key Drivers of Implementation Scale (KDIS) for standardized care processes

Level	Description
0 - No activity	No activity on standardization.
1 - Protocols identified	Practice identifies sample protocols and customizes them for their practice.
2 - Staff enabled	Practice enables staff to perform roles (via standing orders, etc.) needed to implement protocols.

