3 - Testing workflow	Practice is develops/tests workflows to support protocols.
4 - Implementation	Practice implements and follows at least one protocol.
5 - Full implementation	Practice monitors the system to ensure that protocols are used consistently.

*Implementation climate* refers to organizational members’ “shared summary perception of the extent to which their use of a specific innovation is rewarded, supported, and expected within their organization” ([16], p. 1060). We will measure implementation climate using a 6-item scale [17].

*Implementation effectiveness* refers to the consistency and quality of aggregate or pooled innovation use (e.g., evidence-based CVD prevention) [14]. We will assess implementation effectiveness using nine ABCS measures (see Table 3).

**Table 3 Tab3:** Process of care measures for ABCS

Ischemic vascular disease (IVD): use of aspirin or another antithrombotic	Percentage of patients aged 18 years and older with ischemic vascular disease (IVD) with documented use of aspirin or other antithrombotic.
Aspirin for the primary prevention of cardiovascular disease	Percentage of patients between the ages of 50 and 75 with an ASCVD risk score of ≥10 % who do not currently have ischemic vascular disease with documented aspirin use.
Blood pressure management: controlling high blood pressure	Percentage of patients aged 18 through 85 years of age with a diagnosis of hypertension (HTN) whose blood pressure (BP) was adequately controlled (<140/90) during the measurement year.
Blood pressure management: controlling high blood pressure	Percentage of patients aged 18 through 85 years of age with a diagnosis of HTN whose blood pressure was adequately controlled ( age 18–59 and/or people with diabetes or chronic kidney disease <140/90; age 60–85 < 150/90 ) during measurement year.
Statin therapy for prevention and treatment of cardiovascular disease	Percentage of the following patients—all considered at high risk of cardiovascular events—who were prescribed or were on statin therapy: adults ages ≥21 years who were previously diagnosed with or currently have an active diagnosis of clinical atherosclerotic cardiovascular disease (ASCVD); or adults ages ≥21 years with a fasting or direct low-density lipoprotein cholesterol (LDL-C) level ≥190 mg/dL; or adults ages 40–75 years with a diagnosis of diabetes with a fasting or direct LDL-C level of 70–189 mg/dL.

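### The Aim 3 power statement does not follow from its printed inputs, and it is for a model without the calendar trend that the planned analysis keeps

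*Protocol article*

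**What the plan says.** All references are to the protocol article.

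- **Scale.** Under Measures, facilitators' ratings are described thus: "PFs will rate the extent of practice implementation of the four key drivers using a 5-point, behaviorally-anchored scale". Table 2 prints six levels, from 0 up to "5 - Full implementation".
- **Preliminary data.** The Aim 3 power section gives "electronic health record (mean 2.78, sd = 3.17); care protocols (mean 1.71, sd = 4.37); planned care (mean 2.16, sd = 3.84") and "self-management support (mean = 1.38, 3.67"), the last figure evidently also an SD. It continues: "It follows their variances are 10, 19.1, 14.7, and 13.5, respectively".
- **Power model.** Model (5) uses 3-month averages with t = 1 to 4 and an effect covariate (t − 1)/3, so β3 is the whole change from first to last quarter. It sets β3 = 1.0, σ0² = 5 (or 8), σ1² = 4, σ01 = −2 and σe² = 5 (or 8). The variance formula for the outcome uses the same symbol t.
- **Result.** Additional file 3, not at hand, "shows that power to show an effect of intervention on KDIS scales exceeds" 85%.
- **Planned model.** Model (4), in the Aim 3 statistical analysis, keeps g1. The Aim 1 analysis defines g1 as a spline in calendar time for the secular trend under control. Table 1 gives the timing of KDIS ratings as the intervention period only. The power section says that g1 is left out for simplicity.

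**The concern.** The power figure supports Aim 3's primary hypothesis, so a reader should be able to get from the printed assumptions to the printed result. Here the preliminary SDs look too large for the scale, and the variance formula at t = 1 to 4 gives values far beyond anything quoted. The calculation also leaves out the one term in the planned model that competes directly with the effect of interest. If ratings exist only after each practice has started, calendar trend and time since start run together within every practice, and only the staggered start dates can separate them.

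**Working it through.** **1. SDs against the scale.** A score confined to 0–5 with mean m has SD at most √(m(5 − m)).

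| Scale | Mean | Quoted SD | Maximum SD | Quoted SD squared |
|---|---|---|---|---|
| Electronic health record | 2.78 | 3.17 | 2.48 | 10.05 |
| Care protocols | 1.71 | 4.37 | 2.37 | 19.10 |
| Planned care | 2.16 | 3.84 | 2.48 | 14.75 |
| Self-management support | 1.38 | 3.67 | 2.24 | 13.47 |

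The squaring is right. All four SDs exceed the bound, and no variance on 0–5 can exceed 2.5² = 6.25.

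**2. The printed power, quarters coded 1 to 4.** N = 300 is the recruitment target, and two-sided 0.05 is the Aim 1 level. Neither is restated for Aim 3, so both are assumptions.

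- Σ(t − 2.5)² = 2.25 + 0.25 + 0.25 + 2.25 = 5, and β3 is three times the slope per quarter. So Var(β3) = 9(σ1² + σe²/5)/300; σ0² drops out.
- σe² = 5: 9(4 + 1)/300 = 0.150, SE 0.387. Two-sided power Φ(2.582 − 1.960) = 73.3%; one-sided Φ(2.582 − 1.645) = 82.6%.
- σe² = 8: 9(4 + 1.6)/300 = 0.168, SE 0.410. Two-sided power 68.4%; one-sided 78.7%.
- Simulation (4,000 data sets per setting, two-sided) gives 73.5–73.7% and 68.7–69.5%.
- Outcome variance with σ0² = σe² = 5 is 10 + 4t² − 4t = 10, 18, 34, 58 over the four quarters.

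**3. The same parameters with the slope on time scaled 0 to 1.**

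- Σ(x − 0.5)² = 5/9, so Var(β3) = (σ1² + 9σe²/5)/300.
- σe² = 5: 13/300 = 0.0433, SE 0.208, power 99.8%.
- σe² = 8: 18.4/300 = 0.0613, SE 0.248, power 98.1%.
- Outcome variance is 10 at both ends and 9.1 between (σ0² = σe² = 5), or 16 and 15.1 (both 8). These values are close to or inside the quoted 10 to 19.1.

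**4. Keeping g1, taken as linear.** Research design gives starts at months 9, 11 and 12 (50 practices each over both regions) and months 14 and 16 (75 each). Readiness is in the model, so only the spread of start months within a readiness stratum helps.

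- High readiness, mean start 10.67: 50 × (1.67² + 0.33² + 1.33²) = 233.3. Low readiness: 150 × 1² = 150. Total 383.3.
- Within a practice, the ratings identify only the sum of calendar slope and intervention slope. The calendar slope per month must come from comparing practices with different starts. Even with no residual error, its variance is at least (σ0² − σ01²/σ1²)/383.3, that is (5 − 1)/383.3 or (8 − 1)/383.3.
- Over the 11 months from month 1 to month 12, SE(β3) is therefore at least 11√(4/383.3) = 1.12 or 11√(7/383.3) = 1.49. Two-sided power is at most Φ(1/1.12 − 1.96) = 14% or Φ(1/1.49 − 1.96) = 10%, whichever way t is coded.
- The full generalized least squares calculation (monthly ratings, region, readiness and their interaction, linear g1) gives SE about 1.2 to 1.6 and power 10% to 13% with the slope on 0–1. With the slope on 1–4, SE is about 1.4 to 1.8 and power 8% to 11%. Replacing the linear intervention effect by the planned four segments hardly changes this.

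**The case against.** The best defence is that the simulation scaled time from 0 to 1 and the article prints t loosely. The variances in step 3 favour this: they sit near the quoted range, while those from t = 1 to 4 do not. On that reading the claim of more than 85% is true. This stands, and it rules out the stronger inference that Aim 3 really has 68% to 73% power. It does not rescue the text, which prints t = 1 to 4 and no other coding.

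The SDs enter only indirectly, because the calculation uses the variance components. They would be feasible as change scores between −5 and 5, where the bounds at the quoted means are 4.16 to 4.81. Variances that are too large also make a power calculation conservative. All of this stands, so a reader who infers underpowering from the SDs goes too far. But the article presents the figures as KDIS data, not as change.

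N, alpha and sidedness are borrowed, and the alternative is written as β3 > 0. One-sided testing on the printed coding still stays below 85%.

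On g1, the article openly drops the term, and its Aim 3 hypothesis is already a change from month 1 to month 12. The disclosure is fair. It still leaves a power figure for a model that is not the one planned, and the difference is large.

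**Conclusion.** The power statement needs correction on three counts.

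- **SDs.** The quoted values cannot be SDs of a 0–5 score at the quoted means. This is certain given Table 2; what they do measure cannot be told from the article.
- **Power.** On the printed coding it is 68% to 73% two-sided or 79% to 83% one-sided, assuming 300 practices and level 0.05. On a 0–1 time scale it is 98% to 99.8%. A mis-stated unit of t is the likelier explanation, so the finding is an inconsistency, not a demonstrated shortfall.
- **Model.** With a linear g1 kept, power is about 8% to 13% under either coding. This rests on the printed variance components and start months. Smaller, feasible variances would raise it: if the conditional intercept variance were 1 instead of 4 (an illustrative assumption), the ceiling in step 4 would be Φ(1/0.56 − 1.96), about 43%. The planned spline contains a linear trend and can only cost more.

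The difference between a 5-point description and six printed levels is a matter of wording only. Aims 1, 2 and 4 were not examined here.

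**What to change.** 1. Go back to the source of the preliminary figures, say what the quoted SDs measure, and choose variance components that are feasible for the outcome actually modelled.
2. State the unit of t for the random slope, and the N, alpha and sidedness for Aim 3. Rerun the simulation and restate the power.
3. Settle g1. Either remove it from model (4), since there are no control-period ratings, and report the estimate as uncontrolled within-practice change from month 1 to month 12; or keep it and report the power of the model that includes it.
4. Make the description of the scale agree with the six levels in Table 2.

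The cost is one rerun and a few sentences. Dropping g1 makes the Aim 3 claim more descriptive; keeping it means accepting, and stating, a much less precise estimate.

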#### Supplemental analysis

We will use simple statistics to describe the frequency and distribution of positively and negatively coded comments about the acceptability of primary care practice support. We will examine whether acceptability varied by primary care practice support intensity, baseline capacity for QI, and inner and outer contextual features. We will use the qualitative data to explore the reasons why KIs found primary care practice support acceptable (or not) and recommendations they have for future efforts.

#### Aim 4: Evaluate the effect of practice facilitation on practice capacity to implement future evidence-based clinical guidelines

Our primary hypothesis is that primary care practice support will improve capacity to implement other evidence-based clinical guidelines in the future. Our secondary hypotheses are that (a) contextual factors will moderate the effect of primary care practice support on practice capacity to implement additional evidence-based clinical guidelines, and (b) primary care practice support will generate additional positive practice outcomes.

#### Statistical analysis

We will analyze adaptive reserve and change process capability with a linear mixed model applied to the measures collected at baseline (*t* = s_i_), at the end of the intervention period (*t* = s_i_ + 12), and, for the early enrolled practices, at 6 months post-intervention (*t* = s_i_ + 18). The model to assess improvement in these outcomes is a simplification of model (1) because there are only two repeated outcomes:6$$ E\left({Y}_{\mathrm{i}\mathrm{t}}\Big|\ {b}_{\mathrm{i}0,}{b}_{\mathrm{i}1}\right) = {\beta}_0 + {b}_{\mathrm{i}0} + {\beta}_1{X}_{\mathrm{i}1} + {\beta}_2{X}_{\mathrm{i}2} + {\beta}_{12}{X}_{\mathrm{i}1}{X}_{\mathrm{i}2} + {g}_1\left({t}^{*};\uppsi \right) + {b}_{\mathrm{i}1}t + {\beta}_3{X}_{\mathrm{i}\mathrm{t}3}+{\beta}_4{X}_{\mathrm{i}\mathrm{t}4} $$where *X*_it3_ = 1 if *t* = s_i_ + 12 (end-of-intervention period) and *X*_it3_ = 0 otherwise; *X*_it4_ = 1 if *t* = s_i_ + 18 (6 months post-intervention) and baseline is the reference time period. Other assumptions are as in model (4). Primary interest is in *β*_3_, the difference in mean measure between baseline and end-of-intervention period.

In secondary analyses, contextual factors will be examined as additional main effects and as statistical interactions with *X*_it3_ in order to assess whether there are effect modifiers for the effect of primary care practice support on practice capacity to implement future evidence-based clinical guidelines. To test the hypothesis that primary care practice support generated additional positive practice outcomes, we will calculate 95 % confidence intervals for proportions of practices reporting positive outcomes, both overall and stratified by practice characteristics (inner context). We will also use logistic regression to ascertain whether additional positive outcomes varied as a function of primary care practice support intensity, KDIS scores, ABCS measures, and inner context variables.

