#### Provider/staff survey

We will survey providers and staff to assess practice capacity for QI at baseline, end-of-intervention, 6 months post-intervention, and 12 months post-intervention for practices enrolled earlier; organizational readiness to implement change at baseline; and implementation climate at end-of-intervention and 6 months post-intervention. The sample will consist of 3–5 providers and staff members depending on practice size (*N* = 900–1500).

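### The Aim 4 moderation analysis interacts contextual factors only with the month-12 indicator, which ties their month-18 slope to baseline and biases the month-12 interaction toward zero if moderation persists

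*Protocol article*

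**What the plan says.** Aim 4, secondary hypothesis (a), is that "contextual factors will moderate the effect of primary care practice support on practice capacity to implement additional evidence-based clinical guidelines".

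The Aim 4 Statistical analysis section fits model (6) to adaptive reserve and change process capability at s_i and s_i + 12 and, "for the early enrolled practices, at 6 months post-intervention", at s_i + 18. The first indicator is X_it3 = 1 at s_i + 12 ("end-of-intervention period) and *X*_it3_ = 0 otherwise"). The second is X_it4 = 1 at s_i + 18 ("6 months post-intervention) and baseline is the reference time period"). Primary interest is in β3, described as "the difference in mean measure between baseline and end-of-intervention period".

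For moderation, "contextual factors will be examined as additional main effects and as statistical interactions with" X_it3. No factor × X_it4 term is named, and nothing removes month-18 readings from this analysis.

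Two further statements bear on the point:
- The same section introduces model (6) as a simplification for two repeated outcomes, although it lists three time points.
- The Provider/staff survey section plans to "assess practice capacity for QI at baseline, end-of-intervention, 6 months post-intervention" and then adds a 12-month round. Its wording, "6 months post-intervention, and 12 months post-intervention for practices enrolled earlier", can be read as limiting only the 12-month round to early practices.

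**The concern.** With two readings per practice, a factor × X_it3 interaction is the right moderation term: it compares the factor's slope at month 12 with its slope at baseline. With a third reading at which X_it3 is again 0, the factor's main effect has to describe both baseline and month 18. It becomes a weighted average of a pre-support slope and a post-support slope, and the interaction measures month 12 against that average. The model gives month 18 its own mean but not its own factor slope, and the article offers no reason to expect equal slopes before support and six months after it.

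At stake is a missed moderator. Aim 4 concerns capacity for future guidelines, so durable change is what it hopes to find, and durable moderation is where the attenuation is largest. Month-18 moderation itself is not estimated at all under the stated terms.

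**Working it through.** **Plan's own figure.** The only checkable Aim 4 number is the sample size after dropout: 300 × (1 − 0.15) = 255, as stated. The point does not rest on it.

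**Inputs from the protocol article.** The coding of X_it3 and X_it4, the three time points, the named interaction, and the random intercept and slope (all Aim 4 Statistical analysis). High-readiness practices number 75 × 2 = 150 of 300 (Research design). If these are the early enrolled practices, the share f with a month-18 reading is 0.5. On the wider reading of the survey section, f could be 1.

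**Assumed, because the documents do not give them.** A factor fixed at baseline, with the same spread in early and late practices; the persistence r (month-18 moderation divided by month-12 moderation); the Aim 4 variance components.

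**Hand calculation, independent readings.** Let the factor's slope, relative to baseline, be 0 at s_i, δ at s_i + 12 and rδ at s_i + 18. The main effect averages baseline (weight 1) and month 18 (weight f):

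reference slope = f·r·δ / (1 + f), so estimate / δ = 1 − f·r / (1 + f).

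- f = 0.5, r = 1: 1 − 0.5/1.5 = 0.67, understated by 33%.
- f = 1, r = 1: 1 − 1/2 = 0.50, understated by 50%.
- f = 0.5, r = 0.5: 1 − 0.25/1.5 = 0.83, understated by 17%.
- f = 0.25, r = 1: 1 − 0.25/1.25 = 0.80, understated by 20%.
- r = 0: ratio 1, no bias.

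**Correlated readings.** The large-sample generalized least squares limit was computed with readings at 0, 1 and 1.5 years, intraclass correlation 0 to 0.7, slope variance 0 to 0.3 of the baseline variance, and intercept–slope correlation −0.3. Understatement of the factor × X_it3 coefficient:

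| Share with month 18 | r = 1 | r = 0.5 | r = 0 |
|---|---|---|---|
| 0.25 | 16–24% | 8–12% | 0 |
| 0.5 | 29–40% | 15–20% | 0 |
| 0.75 | 41–51% | 20–25% | 0 |
| 1 | 50–59% | 25–29% | 0 |

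Maximum likelihood fits to 20,000 simulated practices (true interaction 0.3, r = 1), with variance components estimated under the planned terms, gave 0.189 to 0.206 at f = 0.5 (32–37% low) and 0.127 to 0.149 at f = 1 (50–58% low).

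**Borrowing the Aim 3 variance components.** With time in years they give 36–39% at f = 0.5 and 56–58% at f = 1. With time in quarters they give 56–59% and 65–66%. The quarterly version implies a variance of 5 + 4·36 − 2·2·6 + 5 = 130 at month 18 (t = 6) against 5 + 5 = 10 at t = 0. They also belong to a different scale, so the size is not rested on them.

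**Standard error and power, independent readings.** The variance of the interaction is proportional to 1 + 1/(1 + f) under the planned terms and to 1 + 1 with factor × X_it4 added. The fix therefore raises the standard error by √(2/1.667) = 1.10 at f = 0.5 and by √(2/1.5) = 1.15 at f = 1. Take a test with 80% power under the full specification (expected z = 1.96 + 0.84 = 2.80). Under the planned terms:
- f = 0.5, r = 1: z = 2.80 × 0.667 × 1.095 = 2.04, power about 53%.
- f = 1, r = 1: z = 2.80 × 0.5 × 1.155 = 1.62, power about 37%.
- f = 0.5, r = 0.5: z = 2.80 × 0.833 × 1.095 = 2.56, power about 72%.
- f = 0.5, r = 0: z = 2.80 × 1.095 = 3.07, power about 87%.

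Over the correlated settings the corresponding powers are 53–57% and 35–37% for the first two and 72–78% for the third. With r = 0 power is 86–93%.

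**After the fix.** With factor × X_it4 added, both interaction coefficients equal their true values in every setting checked.

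**The case against.** The strongest objection is that one sentence in a journal article is not an exclusive specification. It does not say that X_it3 is the only indicator interacted, or that month-18 readings enter the moderation fit. Two cues point to a two-reading analysis: the remark about two repeated outcomes, and the Aim 4 power section, which sets aside the 6-month follow-up. If moderation is fitted to baseline and month 12 alone, there is no bias. This makes the intention uncertain. It does not remove the point, because the section applies model (6) to month-18 readings and names one interaction, which is right for two readings and wrong for three.

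The limits on size and scope stand in full. A reader might infer that month-18 readings are pooled wholesale with baseline; they are not, since β4 gives month 18 its own mean and only the factor slope is constrained. A reader might also infer that moderation is understated by 30–60% whatever happens. The documents do not support that: persistence is not stated, and the upper half of that range generally needs month-18 readings from well over half the practices, whereas the analysis section limits them to early enrolled practices. That group is not defined either, and with a quarter of practices the figure is 16–24% even at full persistence. If moderation has faded by month 18, the constraint does no harm and even gains power.

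Finally, Table 1 collects inner and outer context at baseline, end of intervention and follow-up, so some factors may enter as time-varying. The calculation does not cover that case.

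**Conclusion.** The point holds as a conditional bias in a secondary analysis. As written, the Aim 4 moderation terms force the factor's month-18 slope to equal its baseline slope, and the quantity affected is the month-12 interaction. For a baseline factor, the understatement is about 30–40% if moderation persists fully and about half the practices supply month 18. It is about 15–20% at half persistence with the same share, and zero without persistence. It reaches about 50–60% only if all practices supply month 18 and moderation persists fully. These ranges rest on assumed persistence and variance components.

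It would be wrong to conclude that the primary β3 result is compromised, or that the test is biased when there is no moderation at either time; neither follows. The harm is a true moderator being missed. The structural point is certain from the coding; the size is not. It should be corrected, but it does not threaten the main result of Aim 4.

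**What to change.** In the Aim 4 secondary analyses, enter each contextual factor as a main effect and in interaction with both X_it3 and X_it4. Test the X_it3 interaction for the 12-month effect and report the X_it4 interaction for persistence. Alternatively, state that the moderation model uses baseline and month-12 readings only.

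At the same time, reconcile the description of two repeated outcomes with the three time points listed, and state which practices supply the month-18 reading, since the analysis and survey sections can be read differently.

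The cost is one extra term per factor, or one sentence, and no new data. Adding the X_it4 interaction raises the standard error of the X_it3 interaction by about 8–20% with half the practices at month 18, and by up to about 35% with all. That is the price of dropping a constraint the article does not justify.
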